**Table 27. iRECIST Response Criteria Definitions**

| Response Category                | Criteria                                                                                                                                                                                                                                                                                                  |
|----------------------------------|-----------------------------------------------------------------------------------------------------------------------------------------------------------------------------------------------------------------------------------------------------------------------------------------------------------|
| Immune Complete Response (iCR)   | All lesions resolved                                                                                                                                                                                                                                                                                      |
| Immune Partial Response (iPR)    | At least a 30% decrease in the sum of the diameters of target lesions, taking as reference the baseline sum diameters.                                                                                                                                                                                    |
| Immune Progressive Disease (iPD) | At least a 20% increase in the sum of the diameters of target lesions, taking as reference the smallest sum on study recorded since the treatment started or the appearance of one or more new lesions. In addition to 20% increase, the sum must also demonstrate an absolute increase of at least 5 mm. |
|                                  | Wait up to 12 weeks to confirm PD to account for flare                                                                                                                                                                                                                                                    |
| Immune Stable Disease (iSD)      | Does not meet other criteria                                                                                                                                                                                                                                                                              |

iCPD, immune confirmed progressive disease; iCR, immune complete response; iPR, immune partial response; iSD, immune stable disease; PD, progressive disease.

**Table 28. iRECIST Guidelines for Progressive Disease Evaluation**

| Any factor below on the confirmatory scan (after iUPD) indicates iCPD |                                                                                                                                                                                                                                                                                                                                   |
|-------------------------------------------------------------------------------------|-----------------------------------------------------------------------------------------------------------------------------------------------------------------------------------------------------------------------------------------------------------------------------------------------------------------------------------|
| Target Lesions                                                                      | SOD increases $\geq 5$ mm from iUPD TL
SOD does not have to increase 20% from iUPD                                                                                                                                                                                                                                             |
| Non-Target Lesions                                                                  | Any further increase in size (qualitative assessment) from an iUPD NTL
Does not have to meet 'unequivocal' standard                                                                                                                                                                                                            |
| New Lesions                                                                         | There are any additional new lesions
or
Size of previously detected new lesions increases
- Target NL: NL iSOD increases $\geq 5$ mm
- NT NL: Any significant growth                                                                                                                                           |
| Any factor below indicates progression (iUPD) after iSD/iPR/iCR       |                                                                                                                                                                                                                                                                                                                                   |
| Target Lesions                                                                      | SOD crosses PD threshold (1st time or again)
Based on the nadir (i.e. smallest value ever)                                                                                                                                                                                                                                     |
| Non-Target Lesions                                                                  | New unequivocal progression
or
If already showed PD, and did not regress, any growth                                                                                                                                                                                                                                 |
| New Lesions                                                                         | New lesions of any size appear for the first time, or additional new lesions appear
If new lesions had previously appeared and are still present,
Any growth
- Target NL: NL iSOD increases $\geq 5$ mm
- NT NL: Visible growth
Note: Track nadir for target NL iSOD and total number of new lesions |

TL, target lesion; NTL, non-target lesion; NL, new lesion; NT NL, non-target new lesion; iCPD, immune confirmed progressive disease; iCR, immune complete response; iPR, immune partial response; iSD, immune stable disease; iUPD, immune unconfirmed progressive disease; PD, progressive disease; SOD, sum of diameters for all target lesions; iSOD, immune sum of diameters for new lesion target.

**Statistical considerations for defining the date of iRECIST PD:**

- iUPD subsequently confirmed: The date used is the first iUPD date.
- iUPD never confirmed:
  - If a subsequent iSD, iPR or iCR is seen, the initial iUPD is ignored
  - Otherwise, iUPD date is used

Source: Seymour

[REDACTED]

[REDACTED]

[REDACTED]

|            |            |            |            |
|------------|------------|------------|------------|
| [REDACTED] | [REDACTED] | [REDACTED] | [REDACTED] |
| [REDACTED] |            |            |            |
| [REDACTED] | [REDACTED] | [REDACTED] | [REDACTED] |
| [REDACTED] | [REDACTED] | [REDACTED] | [REDACTED] |
| [REDACTED] | [REDACTED] | [REDACTED] |            |
| [REDACTED] | [REDACTED] | [REDACTED] |            |
| [REDACTED] |            |            |            |
| [REDACTED] | [REDACTED] | [REDACTED] | [REDACTED] |
| [REDACTED] | [REDACTED] | [REDACTED] | [REDACTED] |
| [REDACTED] | [REDACTED] | [REDACTED] | [REDACTED] |

[REDACTED]

## 12.6 Appendix: Management of Infusion Related Reactions

Patients will be monitored closely throughout the entire MP0317 infusion period and will also be questioned closely about any AEs that occur during the 24 hours after the infusion in order to capture any signs and symptoms of IRRs, their timing and recovery.

IRRs are defined by a group of signs and symptoms indicative of hypersensitivity reactions that occur during the 24 hours after the start of the MP0317 infusion and that the Investigator judges as IRRs (e.g. hypersensitivity, allergic reaction, anaphylactic reaction, nausea, vomiting, abdominal pain, headache, hypotension, pyrexia, tremor etc.).

Patients should be treated symptomatically with paracetamol (acetaminophen), ibuprofen (or another antipyretic drug), diphenhydramine (or another antihistamine drug) and/or cimetidine (or another H2 receptor antagonist) and, if considered necessary, corticosteroids, according to institutional standard practice. Serious IRRs manifested by dyspnea, hypotension, wheezing, bronchospasm, tachycardia, reduced oxygen saturation or respiratory distress should be managed with supportive care as clinically indicated (e.g. supplemental oxygen and E2-adrenergic agonists).

The Investigator will ensure that emergency drugs such as noradrenaline and hydrocortisone are readily available in case of IRRs. An emergency resuscitation trolley will also be readily available in case of anaphylactic shock or major cardiovascular events. Supportive care to manage any IRRs will be according to the site's standard-of-care and until the symptoms are resolved.

Guidance for management of IRRs and study treatment modifications are shown in Figure 4, Table 4 and below.

Prophylactic premedication to prevent IRRs may be administered at the discretion of the Investigator. During the second DERC meeting held on 9th March 2022, based on safety data from the first two q3w dosed cohorts, the DERC members strongly recommended prophylactic premedication of patients with antihistamine and paracetamol. Furthermore, based on safety information emerging during the course of the study, the DERC may consider mandating prophylactic premedication to manage IRRs, e.g., by using the regimen detailed below.

To better understand the pathogenesis of IRR, blood samples may be taken to evaluate levels of cytokines, complement factors, drug-specific IgE and tryptase (Table 7, Table 14 and Section 7.4.12).

### Prophylactic Premedication

#### 8 to 16 hours before scheduled MP0317 infusion

- Antihistamine as per SmPC (e.g. loratadine 10 mg, diphenhydramine 50 mg) PO
- Prednisone 1 mg/kg per os (PO)

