### **2.2.3 Exploratory**

- Changes in frequency and functionality of B cells, DC, macrophages and T cell subsets in peripheral blood and tissue biopsies
- Assess FAP and CD40 expression and co-localization with MP0317 in tissue biopsies
- Changes in cytokines in serum
- Changes in sFAP and sCD40 in serum
- Circulating tumor DNA (ctDNA) (safety expansion part only)
- Occurrence of ADAs
- Incidence, titer and time-course of ADAs

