### 6.1 Permitted Therapy for Chronic Diseases and Maintenance Therapy

Stable doses of medications administered for chronic diseases (e.g. hypertension) are allowed. The Investigator must discuss any concomitant therapy with the Sponsor on a case-by-case basis where there is a potential for it to interfere with MP0317 or to alter the interpretation of results.

Systemic corticosteroids and TNF- $\alpha$  inhibitors may attenuate potential beneficial immunologic effects of treatment with MP0317 but may be administered at the discretion of the Investigator after consultation with the Sponsor. If feasible, alternatives to corticosteroids should be considered. The use of inhaled corticosteroids and mineralocorticoids (e.g. fludrocortisone) for patients with orthostatic hypotension or adrenocortical insufficiency is allowed. Megastrol administered as an appetite stimulant is acceptable while the patient is participating in the study. Planned use of other medications should be discussed with the Sponsor.

Hormonal therapy with GnRH agonists or antagonists for prostate cancer, oral contraceptives, hormone-replacement therapy, prophylactic or therapeutic anticoagulation therapy (such as low molecular weight heparin or warfarin at a stable dose level) or other allowed maintenance therapy should be continued.

Males and females of reproductive potential must use highly effective means of contraception (Section 4.2 and Appendix 12.2).

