### 6.3 Prophylactic Premedication

Prophylactic premedication to prevent IRRs may be administered at the discretion of the Investigator. During the second DERC meeting held on 9th March 2022, based on safety data from the first two q3w dosed cohorts, the DERC members strongly recommended prophylactic premedication of patients with antihistamine and paracetamol. Furthermore, based on safety information emerging

during the course of the study, the DERC may consider mandating prophylactic premedication to manage IRRs, e.g., by using the regimen detailed in Appendix 12.6.

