**Table 8. Schedule of Assessments: Cycle 1 Detailed (Q3W)**

|         | Assessment Time Point               | Physical Examination | Vital Signs and Pulse Oximetry | ECG a | Local Laboratory Safety Assessments, Pregnancy Test b , Urinalysis b | PK (Serum)   | Immunogenicity (ADA, Serum) | Blood Biomarkers (Serum, Plasma and/or Fresh Blood) | Skin Biopsy    |
|---------|-------------------------------------|----------------------|--------------------------------|------------------|--------------------------------------------------------------------------------------------|--------------|-----------------------------|-----------------------------------------------------|----------------|
| Cycle 1 | Day 1, before start of infusion     | X                    | X (max -2 h)                   | X (max -2 h)     | X (max -48 h)                                                                              | X (max -2 h) | X (max -2 h)                | X (max -2 h)                                        |                |
|         | Day 1, start of infusion            |                      | X (± 15 min)                   |                  |                                                                                            |              |                             |                                                     |                |
|         | Day 1, during infusion every 30 min |                      | X (± 15 min)                   |                  |                                                                                            |              |                             |                                                     |                |
|         | Day 1, EOI                          |                      | X (± 15 min)                   |                  |                                                                                            |              |                             |                                                     |                |
|         | Day 1, EOI + 15 min                 |                      |                                |                  |                                                                                            | X (± 10 min) |                             | X (± 10 min)                                        |                |

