#### 60 minutes before scheduled MP0317 infusion

- Antihistamine as per SmPC (e.g. loratadine 10 mg, diphenhydramine 50 mg) PO or IV
- Paracetamol 1 g PO or IV

Optional: Prednisone 1 mg/kg PO or methylprednisolone 0.8 mg/kg IV

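### If the steroid premedication in Appendix 12.6 is used before Cycle 1, the only pre-treatment blood biomarker sample is drawn 6 to 16 h after prednisone

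*Protocol*

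**What the plan says.** **Premedication.** Appendix 12.6 states: "Prophylactic premedication to prevent IRRs may be administered at the discretion of the Investigator". Section 6.3 says the same. Both report that in March 2022, after the first two q3w cohorts, the dose-escalation committee (DERC) strongly recommended an antihistamine and paracetamol. No steroid is named there. Section 6.3 adds that "the DERC may consider mandating prophylactic premedication to manage IRRs, e.g., by using the regimen detailed in Appendix 12.6".

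The regimen in Appendix 12.6 has two time points. The first is "8 to 16 hours before scheduled MP0317 infusion" and consists of an antihistamine and oral prednisone 1 mg/kg. The second is 60 minutes before infusion and consists of an antihistamine and paracetamol, followed by this line: "Optional: Prednisone 1 mg/kg PO or methylprednisolone 0.8 mg/kg IV". The earlier prednisone dose carries no such label.

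**Steroids in general.** Section 6.1 says that systemic corticosteroids "may attenuate potential beneficial immunologic effects of treatment with MP0317". It leaves them to the Investigator after consulting the Sponsor and prefers alternatives where feasible.

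**Sampling.** The blood biomarker rows of Table 7 (q3w) and Table 14 (q1w) are empty at screening. The first sample in Tables 8 and 15 is Cycle 1 Day 1 before infusion, with a limit of 2 h. The same rows allow Day 1 safety laboratories up to 48 h before infusion.

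**Endpoint.** Section 2.2.3 lists "Changes in frequency and functionality of B cells, DC, macrophages and T cell subsets in peripheral blood and tissue biopsies", together with changes in serum cytokines.

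**The concern.** The blood pharmacodynamic endpoints are changes from a pre-treatment value, and each patient has only one such value. Nothing in the protocol ties that draw to the timing of premedication. A patient given the steroid regimen before Cycle 1 has a baseline taken after a drug that the protocol itself expects to act on the system being measured. A patient without it has a steroid-free baseline.

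Use is discretionary now and could be mandated part-way through. The mix of exposed and unexposed baselines could therefore follow site or cohort, and so dose level.

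Section 1.3.4 intends these markers to confirm the mode of action and relate exposure to effect. Section 8.5 puts pharmacodynamic information before the DERC. A baseline that was not drawn cannot be recovered at the analysis stage, so this is a matter for the protocol and cannot be left to the SAP.

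**Working it through.** The plan states no figure for this point, so there is none to reproduce. The check is interval arithmetic and a count of scheduled samples. Time 0 is the start of infusion.

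**1. Prednisone to baseline sample**
- Prednisone: -16 h to -8 h (Appendix 12.6).
- Baseline blood biomarker sample: -2 h to 0 h (Tables 8 and 15).
- Shortest interval: (-2) - (-8) = 6 h. Longest interval: 0 - (-16) = 16 h.

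The result is **6 to 16 h**, the same on q3w and q1w because the baseline window is the same.

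**2. Optional steroid dose to baseline sample**
- Dose at -1 h; sample at -2 h to 0 h.
- (-2) - (-1) = -1 h and 0 - (-1) = +1 h.

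The sample may be drawn up to 1 h before or up to 1 h after this dose.

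**3. Pre-dose samples among all blood biomarker samples, Cycles 1 to 5** (Tables 8 to 12 for q3w, Tables 15 to 19 for q1w)

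| Cycle | q3w pre-dose / all | q1w pre-dose / all |
|---|---|---|
| 1 | 1 / 9 | 3 / 9 |
| 2 | 1 / 4 | 3 / 4 |
| 3 | 1 / 4 | 3 / 3 |
| 4 | 1 / 2 | 2 / 2 |
| 5 | 1 / 1 | 1 / 1 |
| **Total** | **5 / 20** | **12 / 19** |

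If the regimen is given before every infusion, each pre-dose sample lies 6 to 16 h after prednisone.

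**4. Day 8 and Day 15 of Cycle 1**
- On q1w both samples are pre-dose, so 6 to 16 h after prednisone.
- On q3w they are 168 h and 336 h after the end of infusion, each ± 4 h. The infusion lasts from 50 min to 2 h. Counting from the prednisone given before Day 1:
  - Day 8: from 168 - 4 + 8 + 0.83 = 172.8 h to 168 + 4 + 16 + 2 = 190 h.
  - Day 15: from 336 - 4 + 8 + 0.83 = 340.8 h to 336 + 4 + 16 + 2 = 358 h.

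On q3w these samples are roughly 7 and 14 days after steroid.

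**5. Counting all samples on dosing days**

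Samples taken after infusion on a dosing day also follow premedication, so pre-dose counts alone understate exposure on both schedules. Counting every dosing-day sample over Cycles 1 to 5:
- q3w: 3 + 2 + 2 + 1 + 1 = 9 of 20.
- q1w: 5 + 4 + 3 + 2 + 1 = 15 of 19.

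The direction is unchanged.

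**The case against.** The strongest reply is that no patient need receive this regimen. Premedication is discretionary, the DERC's actual recommendation contains no steroid, and the prednisone regimen is only an example of what might be mandated. That stands. A reader might infer that baselines in this trial are taken under steroid; the protocol supports this only for patients given that regimen before Cycle 1.

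Four other stronger readings are tempting and are not supported:
- **The baseline differs by schedule.** It does not. Tables 8 and 15 use the same window; only the later samples differ.
- **The regimen breaches the 10 mg/day prednisone limit.** That figure applies to continuous use at entry (Section 4.3) and to steroid reduction after an immune-related event (Table 4, footnote a). Neither governs intermittent premedication.
- **A planned q3w versus q1w comparison is biased.** No such comparison is planned. Section 5.2.7 treats the schedules independently, and Section 9.11 is descriptive. What remains is that informal reading across schedules would be hampered.
- **Recovery from steroid would pass for a drug effect.** This is possible, but the protocol gives no size or time course for it.

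It can also be said that Section 6 already records concomitant medication. It lists reason, dates, dose, frequency and route, but no clock time, so the steroid-to-sample interval could not be reliably reconstructed from that minimum. Splitting summaries by exposure can indeed go in the SAP; the timing of the draw cannot.

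On Section 6.1, one may argue that a DERC mandate already involves the Sponsor, who has the final decision (Section 8.5). That answers the case of a mandate. It does not cover steroid premedication given at an Investigator's own discretion, where Section 6.3 and Appendix 12.6 mention no consultation.

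**Conclusion.** The point holds conditionally. If the steroid regimen of Appendix 12.6 is used before Cycle 1, the sole pre-treatment blood biomarker sample is drawn 6 to 16 h after prednisone 1 mg/kg, and baselines may mix exposed and unexposed patients across sites and cohorts. If the regimen is repeated before every infusion, post-steroid pre-dose sampling is more frequent on q1w (12 of 19) than on q3w (5 of 20).

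The consequence is limited to the exploratory blood pharmacodynamic endpoints. Tumor and skin baselines are taken during screening, and the DLT, safety and PK analyses do not rest on this sample. The conclusion assumes that the regimen is used as written. The documents do not show how often that will be, nor how far steroid shifts these markers. This is a cheap improvement to sampling and does not undermine the trial's main objectives.

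**What to change.** - **Baseline draw.** Where steroid premedication is planned for Cycle 1, require the baseline blood biomarker sample before the first premedication dose, within the 48 h pre-infusion window that Tables 8 and 15 already allow for safety laboratories. Otherwise keep the 2 h limit.
- **Recording.** Capture the clock time of each steroid premedication dose, in addition to the items listed in Section 6.
- **Presentation.** Show blood biomarker change by steroid exposure.
- **Reconciliation.** State how the Sponsor consultation on systemic steroids in Section 6.1 applies to premedication given at Investigator discretion under Section 6.3 and Appendix 12.6. No change to the premedication regimen is proposed, and no view is taken on which passage should prevail.

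**Cost.** There is no additional blood sample: the change is to a sampling window, one recorded time per dose and one split in the summaries. Some patients would be drawn the day before infusion, and their baseline window would differ from that of the cohorts already dosed. That difference should be noted when the data are presented.
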